## Study treatments

The rapid micro-induction arm will involve the administration of buprenorphine/naloxone and hydromorphone, while the standard induction arm will involve the administration of only buprenorphine/naloxone.

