### Hydromorphone

Hydromorphone is an opioid medication used for managing pain, craving, and withdrawal in this study. The opioids the patients are using will be rotated to hydromorphone. Hydromorphone will be administered as needed to meet the patient’s opioid requirements. It will be administered orally via tablet form; or administered intravenously, subcutaneously, or intramuscularly via liquid form. The route of administration will be determined by the physician in charge in consultation with the patient*.*

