### Medical management

In both the standard induction and rapid micro-induction arms, residual withdrawal symptoms will be managed as per ASAM guidelines: clonidine may be used at doses of 0.1–0.3 mg every 6–8 h, with a maximum dose of 1.2 mg daily (American Society of Addiction Medicine, 2020). Other non-narcotic medications targeting specific opioid withdrawal symptoms can also be used as per ASAM guidelines: benzodiazepines for anxiety, loperamide or bismuthsalycilate for diarrhea, acetaminophen or non-steroidal anti-inflammatory medications (NSAIDs) for pain, zopiclone for insomnia, and ondansetron for nausea.

All participants will receive routine motivational interviewing, behavioural-based psychoeducation, and supportive psychotherapy provided by the CPAS team based on the individual’s need. The type, duration, and reason for all the psychological interventions and medications provided will be documented in the case report form (CRF).

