### Secondary outcomes

The secondary outcomes are treatment retention, illicit drug use, self-reported drug use behaviour, craving, pain, physical health, safety, and client satisfaction.

Treatment retention will be assessed by buprenorphine/naloxone prescription pick-up on day 7.

Illicit drug use will be assessed by urine drug screens, which will analyze for the presence of cocaine, opioids including methadone, buprenorphine, hydromorphone, oxycodone, morphine, heroin, and fentanyl, benzodiazepines, amphetamines, and methamphetamine. Urine will be collected at screening, baseline, and after induction has been completed (day 3 of the experimental arm, and day 2 of the control arm).

Self-reported drug use behaviour will be assessed by the Treatment Outcome Profile (TOP) at baseline, and after induction has been completed (day 3 of the experimental arm, and day 2 of the control arm). The TOP is a 20-item instrument designed to assess and monitor substance misuse by measuring four different domains (substance use, health, crime and social functioning) and includes thirty-eight frequency, rating scale and period prevalence measure [30].

Craving and pain will be measured by numeric rating scales (NRS) at baseline, days 1 to 2 of the experimental arm, and day 1 of the control arm. The NRS for craving and pain will be administered every time the COWS is administered. The NRS presents the participant a rating scale which represents the spectrum of pain or craving: the left end indicates no pain or craving while the right end indicates extreme pain or craving [31]. Participants rate their pain or craving from 0 to 10.

Physical health will be assessed by the health section of the Opiate Treatment Index (OTI) at baseline. The OTI is a structured interview designed to provide a measure of the effectiveness of drug treatments, by measuring six outcomes: drug use, HIV risk-taking behaviour, social functioning, criminality, health status, and psychological functioning [32]. Only the health section of the OTI will be used; the health section is composed of items addressing signs and symptoms in major organ systems and injection-related health problems.

Safety will be assessed by the appearance of adverse events (AEs) and serious adverse events (SAEs), which will be recorded on the CRF. AEs and SAEs are defined in “Safety” section.

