We believe that the findings from this study will be generalizable to clinical settings in many jurisdictions, including settings with patients who use fentanyl. In British Columbia, there has been a surge in fentanyl-detected overdose deaths, as fentanyl was only detected in 5% of illicit drug deaths in 2012 but was detected in 87% of the deaths in 2019 [35]. Deaths involving fentanyl have also rapidly increased across many states in the United States [36, 37]. Furthermore, buprenorphine for the treatment of OUD has become increasingly available in the United States [25]. A limitation in our study is the administration of hydromorphone during the first 2 days of the rapid micro-induction arm, as some jurisdictions may face regulatory barriers when using hydromorphone with the induction method. However, it should be noted that in the context of the study, hydromorphone is used on an as-needed basis to meet the patient’s opioid requirements during the induction process. In clinical practice, we use the rapid micro-induction method with any opioid based on the patient’s preferences and clinical indications. We plan to conduct future studies where patients on methadone are not excluded and other opioids are used instead of hydromorphone.

The open-label design of this clinical trial may also introduce the risk of potential bias. However, it is not feasible to blind participants or researchers due to the nature of the interventions. The study may also benefit from a large sample size and a longer duration of follow-up, but such changes are not possible due to resource and cost constraints. Despite these limitations, the evaluation of the primary and secondary outcomes will greatly contribute to our understanding of rapid micro-induction. As the opioid crisis in North America continues, the results derived from this clinical trial will generate the first major body of clinical evidence on the effectiveness and safety of rapid micro-induction, a novel and patient-centered induction approach which could immensely improve the accessibility of buprenorphine/naloxone for patients with OUD.

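### The urine-screen list for illicit drug use includes hydromorphone, which the trial supplies to one arm only, and buprenorphine, which it supplies to both, and does not set either aside

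*Protocol article*

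**What the plan says.** All references are to the protocol article.

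- **Outcome definition (Secondary outcomes, under Outcomes and assessments).** The illicit-use outcome is measured by screens of urine, "which will analyze for the presence of cocaine, opioids including methadone, buprenorphine, hydromorphone, oxycodone, morphine, heroin, and fentanyl". Further drugs follow in the list, among them benzodiazepines.
- **Treatment by arm (Study treatments).** The article sets the arms apart in one sentence: "The rapid micro-induction arm will involve the administration of buprenorphine/naloxone and hydromorphone, while the standard induction arm will involve the administration of only buprenorphine/naloxone".
- **Hydromorphone use (Hydromorphone; Table 1; Discussion).** "Hydromorphone will be administered as needed to meet the patient’s opioid requirements". Table 1 allows it on days 1 and 2 and lists it as discontinued from day 3. The Discussion names "A limitation in our study is the administration of hydromorphone during the first 2 days of the rapid micro-induction arm", but as a matter of generalisability to places with regulatory barriers, not of outcome measurement.
- **Sampling (Secondary outcomes; Table 3).** Besides screening and baseline, urine is taken "after induction has been completed (day 3 of the experimental arm, and day 2 of the control arm").
- **Other permitted drugs (Medical management).** The list for both arms includes "benzodiazepines for anxiety". The same section has all medications provided recorded in the case report form (CRF).
- **Comparison (Data analysis, Secondary outcomes).** Secondary outcomes are compared between arms by a method that depends on the type of variable.

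No section says that a positive explained by trial treatment or a prescription is left out of the illicit-use outcome.

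**The concern.** An outcome called illicit drug use should register use outside treatment. Here the list of target drugs overlaps with the drugs the trial gives, and for hydromorphone the overlap differs by arm. The same laboratory result would mean assigned treatment in one arm and non-prescribed use in the other. Randomisation cannot balance this, because allocation itself causes it. The error goes against the experimental arm.

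Illicit drug use is a named secondary objective, and the urine screen is its only laboratory measure; the other drug-use outcome is self-reported. A misleading difference, or a real one hidden, would bear on how micro-induction is judged.

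**Working it through.** The plan states no figure for this outcome, so there is none to reproduce. The check has two parts.

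**1. What a post-induction positive means, drug by drug**

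| Drug on the screen | Experimental arm, day 3 | Control arm, day 2 | Use for the comparison |
|---|---|---|---|
| Hydromorphone | May be trial treatment from days 1–2 | Non-prescribed, unless the participant switched arms | Biased against micro-induction |
| Buprenorphine | Trial treatment | Trial treatment | No information on illicit use |
| Benzodiazepines | May be prescribed | May be prescribed | Blurred in both arms under the same rule |
| Cocaine, fentanyl, heroin, amphetamines, methamphetamine | Not study treatment | Not study treatment | Valid if reported separately |

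By Table 1, the experimental sample falls in the 48–72 h period, which begins when the hydromorphone period ends at 48 h.

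**2. Size of the hydromorphone artefact**

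Inputs:
- 25 per arm (Sample size and power calculation).
- Two-sided Fisher's exact test at 0.05. The protocol states this level for the primary outcome; its use here, and two-sidedness, are assumptions.
- p = true illicit-use rate, set equal in both arms. Assumed: 0.2, 0.4, 0.6.
- h = share of the experimental arm still positive on day 3 from trial hydromorphone, independent of illicit use. Assumed: 0 to 100%, because dosing is as needed and the article gives neither the exposed share nor a detection window.

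Formulas:
- Control positive rate = p
- Experimental positive rate = 1 − (1 − p)(1 − h)
- False difference = 1 − (1 − p)(1 − h) − p = h(1 − p)

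Example: p = 0.2 and h = 0.5 give 1 − 0.8 × 0.5 = 0.60 against 0.20, a false difference of 40 points.

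Each cell shows the false difference in points, then the share of trials in which the test rejects (exact enumeration):

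| p | h = 0 | h = 25% | h = 50% | h = 75% | h = 100% |
|---|---|---|---|---|---|
| 0.2 | 0; 2.2% | 20; 23% | 40; 79% | 60; 99% | 80; 100% |
| 0.4 | 0; 3.0% | 15; 14% | 30; 51% | 45; 89% | 60; 100% |
| 0.6 | 0; 3.0% | 10; 7% | 20; 23% | 30; 59% | 40; 97% |

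The column h = 0 is the outcome with trial hydromorphone not counted: rejection stays below the nominal 5%.

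If control participants who switch arms also turn positive from trial hydromorphone, in share c, the false difference becomes (1 − p)(h − c). Switching shrinks the artefact but does not remove it while h exceeds c.

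If a buprenorphine positive also counted and every treated participant tested positive (assumption), both arms would stand at 100% and the test could never reject.

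**The case against.** The strongest reply is that a list of drugs assayed is not a scoring rule. The text says what the laboratory looks for, not that every positive is an outcome event. The screen has other purposes, since a positive methadone screen excludes a patient. On an ordinary reading a drug prescribed in the trial is not illicit, and a full protocol or analysis plan may say so. This stands in part, and is why the finding is conditional on scoring as listed. It does not dispose of the point: the published definition itself places study drugs inside the illicit-use measure, and nothing in the article takes them out.

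A reader might infer several stronger claims that the article does not support:

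- **That the plan applies Fisher's test to a pooled any-drug result.** Data analysis names three methods by variable type and assigns none to this outcome; no pooled score is defined. The rejection rates above are illustrations.
- **That the false difference is about 100 points.** This is only the limit of h(1 − p), with everyone positive from trial hydromorphone and no true use. Hydromorphone is as needed, and day-3 detectability is not documented.
- **That control participants never receive hydromorphone.** Those who stop their assigned treatment are offered the other one, and their data may still be collected.
- **That the whole outcome measures study treatment.** Several listed drugs are not study treatment and stay informative one by one.
- **That benzodiazepines bias the comparison between arms.** They are permitted under the same rule in both, and no imbalance is shown.

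The different sampling days are a separate matter, which the article explains by the different lengths of the two inductions; this point does not depend on changing them.

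**Conclusion.** The point holds in conditional form. Scored as listed, the illicit-use outcome is biased against micro-induction wherever hydromorphone, or any opioid, is counted, and buprenorphine contributes nothing to it. The direction follows from the treatment schedule as long as more experimental than control participants are positive from trial hydromorphone. The size does not follow from the document. At a true rate of 20% in both arms it is 20 to 80 points for h of 25% to 100%; at 60% it is 10 to 40 points. These figures rest on assumed p and h, equal true use, independence of the two sources of a positive, and no switching.

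Severity is moderate. This is one secondary outcome; the primary outcome, its test and the sample size are untouched.

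**What to change.** Amend the outcome definition, in the protocol or the analysis plan, to say that:

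- illicit drug use is defined on drugs not supplied or prescribed in the trial;
- hydromorphone and buprenorphine are removed from it in both arms and reported separately as exposure;
- benzodiazepines and other opioids count only when the CRF medication record shows no prescription;
- drugs such as cocaine, fentanyl, heroin, amphetamines and methamphetamine are reported separately.

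The cost is a few sentences. No new data are needed, because the CRF already records medications provided, and no treatment rule changes. The downside is that non-prescribed hydromorphone or buprenorphine use is no longer counted in either arm.

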**Fig. 1 Fig1:**
[figure not shown]
Study schema

Eligible participants will be randomized on an allocation ratio of 1:1 to either of the two arms, using a blocked permuted block design with block sizes of 4 and 6. Randomization will be managed with the REDCap platform [23, 24]. Once randomized, participants will complete baseline assessments and be followed for 7 days. Towards the end of the intervention period, the physician in charge will inform all participants about follow-up treatments that are available to them. Participants will receive follow-up with their community addictions physicians and/or the CPAS outpatient clinic.

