### Study objectives

The primary objective is to compare rapid micro-induction versus standard induction on the successful induction of buprenorphine/naloxone with low levels of withdrawal in patients with OUD. The secondary objectives are to evaluate treatment retention, illicit drug use, self-reported drug use behaviour, craving, pain, physical health, safety, and client satisfaction.

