## Outcomes and assessments

The timeline of assessments is shown in Table 3. It should be noted that there is an additional day of assessments conducted with the experimental arm, because the experimental intervention (rapid micro-induction) takes one day longer than the treatment-as-usual intervention (standard induction).

**Table 3 Tab3:** Timeline of assessments

Assessments	Screening	Randomization	Baseline^d^	Day 1^d^	Day 2	Day 3	Day 4	Day 7
Experimental arm: rapid micro-induction (E stands for experimental arm assessments)								
Control arm: standard induction (C stands for control arm assessments)								
Informed consent form	E C							
Physical examination	E C		E C	E C	E C	E C	E	
Medical history	E C							
Pregnancy test	E C							
Blood tests^a^	E C							
Viral profile^b^	E C							
Urine drug screens	E C		E C		C	E		
Opiate treatment index (OTI)—health section			E C					
Treatment outcomes profile (TOP)			E C		C	E		
Clinical Opiate Withdrawal Scale (COWS)			E^c^ C^c^	E^c^ C^c^	E^c^			
Numeric Rating Scale for craving			E^c^ C^c^	E^c^ C^c^	E^c^			
Numeric Rating Scale for pain			E^c^ C^c^	E^c^ C^c^	E^c^			
Treatment Perceptions Questionnaire (TPQ)					C	E		
Assessment of treatment retention								E C
Adverse event report form			E C	E C	E C	E C	E	

^a^Complete blood count (CBC), Extended lytes, Liver function

^b^HepC serology, HepB antigen, HIV Elisa

^c^The COWS and Numeric Rating Scales for craving and pain will be administered at baseline, every 1.5 h during the abstinence period (control arm only), and throughout the induction process for both arms (days 1 to 2 of the experimental arm, and day 1 of the control arm)—specifically, immediately before each dose of buprenorphine/naloxone, and 1 to 1.5 h after each dose of buprenorphine/naloxone

^d^Baseline and day 1 assessments may be done on the same day, depending on the time of day the participants are recruited in the study and the state they are in when they are recruited

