### Secondary outcomes

Secondary outcomes will be compared between two arms using Fisher’s exact, Wilcoxon–Mann Whitney, and interaction terms from Linear Mixed Models for binary, interval, and repeated measures, respectively.

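### Physical health is listed as a secondary outcome to be compared between arms, but its only instrument is given once, at baseline

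*Protocol article*

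**What the plan says.** Physical health appears in the outcome list of the abstract (Methods) and again in two sections of the article:

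- Study objectives: "The secondary objectives are to evaluate treatment retention, illicit drug use, self-reported drug use behaviour, craving, pain, physical health, safety, and client satisfaction".
- Outcomes and assessments, Secondary outcomes: "The secondary outcomes are treatment retention, illicit drug use, self-reported drug use behaviour, craving, pain, physical health, safety, and client satisfaction".

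The same Secondary outcomes section gives the one measure and its one time point: "Physical health will be assessed by the health section of the Opiate Treatment Index (OTI) at baseline". In Table 3 the row "Opiate treatment index (OTI)—health section" has an entry for both arms in the baseline column and is empty for days 1, 2, 3, 4 and 7.

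Under Data analysis, Secondary outcomes, the article says: "Secondary outcomes will be compared between two arms using". It then names Fisher's exact test, the Wilcoxon-Mann-Whitney test, and interaction terms from linear mixed models, according to the type of variable. Physical health is not exempted.

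**The concern.** An outcome compared between randomized arms must be measured at a time when treatment could have affected it. Here the only value is a baseline value. The test would address whether the arms were alike at the start, not whether rapid micro-induction and standard induction differ in their effect on physical health.

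Two things are at stake. One of the eight stated secondary objectives cannot be answered with the data the schedule collects. And a comparison run as written yields a p-value, under an outcome label, that has no treatment effect in it. If that p-value happened to be small, it could be misread as a finding about treatment.

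**Working it through.** The article gives no figure to reproduce for this point. The check is to set the outcome list against the schedule, and then ask what each named method could do with the data.

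**1. When each secondary outcome is measured (Table 3 and Secondary outcomes text)**

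| Secondary outcome | Named measure | Data during or after treatment? |
|---|---|---|
| Treatment retention | Prescription pick-up | Yes, day 7 |
| Illicit drug use | Urine drug screen | Yes, day 3 (experimental), day 2 (control) |
| Self-reported drug use | TOP | Yes, day 3 / day 2 |
| Craving | Numeric rating scale | Yes, during induction |
| Pain | Numeric rating scale | Yes, during induction |
| Physical health | OTI health section | **No, baseline only** |
| Safety | Adverse events | Yes, to day 4 / day 3 |
| Client satisfaction | TPQ | Yes, day 3 / day 2 |

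Seven of eight have data from the treatment period or later; physical health has none. The contrast shows within the same section, where the wording for the TOP is "Self-reported drug use behaviour will be assessed by the Treatment Outcome Profile (TOP) at baseline, and after induction has been completed". Text and table agree on the OTI, so this is neither a slip in one place nor a damaged table.

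**2. Whether baseline could contain a treatment effect**

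Baseline follows allocation: "Once randomized, participants will complete baseline assessments and be followed for 7 days". A footnote to Table 3 adds: "Baseline and day 1 assessments may be done on the same day". Baseline nevertheless keeps its own column, separate from day 1, and I take it to precede the first study dose. Because the trial is open-label, a baseline interview held after randomization could be coloured by knowledge of the arm. A baseline difference could therefore reflect chance or that knowledge, but not an effect of the study drugs.

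**3. What the planned methods can do**

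- *Fisher or Wilcoxon-Mann-Whitney on the OTI score.* This compares baseline values only.
- *Mixed-model interaction.* An arm-by-time term needs at least two time points. There is one, so the term cannot be estimated.

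**4. Illustration of size**

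Inputs: 25 per arm (Sample size and power calculation); two-sided 0.05 (stated for the primary test, assumed here for a secondary one); baseline scores independent of arm (assumed); 4000 simulated trials per setting; Wilcoxon-Mann-Whitney test. The article gives no OTI effect or SD, so the true post-induction effect was varied from 0 to 1.0 SD, with an assumed baseline/post correlation of 0.5.

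| True later effect (SD) | Rejections, baseline only | Rejections, one post-induction score |
|---|---|---|
| 0 | 5.0% | 4.8% |
| 0.5 | 4.5% | 37.9% |
| 0.8 | 4.6% | 77.1% |
| 1.0 | 4.7% | 92.0% |

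The simulation error of a 5% rate is √(0.05 × 0.95 / 4000) = 0.34 percentage points, so the middle column is flat at about the nominal level. The last column, which is not adjusted for baseline, agrees roughly with the normal approximation Φ(d√(25/2) − 1.96). For d = 0.5 this is Φ(1.77 − 1.96) = 42%; for d = 0.8 it is 81%; for d = 1.0 it is 94%. These power figures depend on the assumed effects. They show only that a later measurement can carry information on treatment, whereas the baseline one cannot.

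**The case against.** The strongest reply is that this is a baseline descriptor placed in the wrong list. The article openly labels the measurement as baseline, and the objectives speak of comparing for the primary outcome but only of evaluating for the secondary ones. Nothing in the text says that a baseline score will be presented as a treatment effect, so that harm is a risk and not a certainty. This stands, and it limits the claim. It does not remove the inconsistency, because the data analysis section compares secondary outcomes between arms and makes no exception.

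A second reply is that later health information exists. Physical examinations and adverse event reports continue to day 3 (control) or day 4 (experimental), and the TOP has a health domain that is repeated after induction. That is true and limits the practical loss. None of these is designated as the physical health measure, however, and the TOP is assigned to drug use behaviour.

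A third reply concerns repeating the OTI two or three days later. The article gives no recall period and no evidence that the health section responds over so short a time, and the post-induction days differ between arms. This also stands, and it is a reason to prefer relabelling.

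Finally, the 5% rate merely restates the significance level. That is fair: the substantive size of the problem is zero post-treatment measurements.

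**Conclusion.** The concern holds. As written, the plan includes a between-arm comparison of physical health with no post-treatment data in either arm, and one of eight secondary objectives cannot be answered with the named instrument. This follows from the text and Table 3 together. It assumes only that baseline precedes the first study dose and that no other measure is meant to stand for physical health; the article names none. A separate analysis plan could not repair it, because it cannot analyse data that the schedule does not collect. The primary outcome, its analysis and the sample size are untouched. The point should be corrected, but it does not threaten the trial's main conclusion.

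**What to change.** Choose one of two changes.

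1. **Relabel (preferred).** List the OTI health section as a baseline characteristic and remove physical health from the outcome lists in the abstract and Secondary outcomes, and from Study objectives. Summarise it by arm without a test. This costs a wording change and no data collection.

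2. **Measure it after induction.** Add the OTI health section where the TOP and TPQ are already given (day 3 experimental, day 2 control), and compare arms adjusted for the baseline score. This costs one more section of a structured interview at an existing assessment; the article does not give its length. Before choosing this, the investigators should confirm that the instrument can register change over two to three days, and should address the one-day difference in timing between arms.

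The section on current status describes the site as still preparing for recruitment in November 2020, so at that point either change could have been made before any participant was enrolled.
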